## Abstract

**Background:**

Approximately 5% of adults have an episode of acute bronchitis each year, accounting for more than 10 million medical visits yearly. The primary goal of treatment is reduction of symptoms. Currently, available medications are questionable in effectiveness and safety and are not recommended for routine use in clinical practice. Although Chinese herbal medicine has been widely used in the management of acute bronchitis in China, evidence-based data is lacking. This trial aims to evaluate the efficacy and safety of Tanreqing oral liquid in the treatment of acute bronchitis with phlegm-heat obstructing lungs syndrome.

**Methods/design:**

This study is a prospective, multi-center, randomized, double-blinded, parallel-group, placebo-controlled trial. A total of 270 acute bronchitis adult patients with phlegm-heat obstructing lungs syndrome will be enrolled from outpatients and emergency departments at nine study centers across China. All included patients will be randomly allocated to receive Tanreqing oral liquid or placebo oral liquid, 20 mL three times daily for seven consecutive days. The primary outcome will be cough resolution rate. Secondary outcomes will include change of bronchitis symptoms scores from baseline to post-treatment, cough relief rate, time to cough resolution, time to cough relief, resolution rate of a single symptom, combination medicine use, change of traditional Chinese medicine syndrome score from baseline to post-treatment, and adverse events.

**Discussion:**

This trial may provide an alternative treatment option for acute bronchitis patients, especially those in outpatients and emergency departments. It may also add evidence to Chinese herbal medicine for treating acute bronchitis.

**Trial registration:**

Chinese Clinical Trial Registry ChiCTR2000040264. Registered on 26 November 2020

**Supplementary Information:**

The online version contains supplementary material available at 10.1186/s13063-022-06318-5.

## Background

Acute bronchitis (AB) is a common clinical condition characterized by acute inflammation of the trachea and lower airways. About 95% of uncomplicated AB patients are caused by viral infections, and bacterial infections are not common [1, 2]. Approximately 5% of adults have an episode of AB per year, accounting for more than 10 million medical visits each year [3]. Patients predominantly present with cough with or without sputum production without evidence of pneumonia. Cough usually lasts no more than 3 weeks and is the major reason for both outpatients consultations and emergency departments attendances.

Although AB is considered to be self-limiting in most cases, symptomatic treatment is primarily required, particularly improving cough. Antibiotic agents have been widely but unnecessarily used worldwide. However, antibiotics use can only provide a modest reduction of cough duration by 0.46 days, and unnecessary antibiotics use may be associated with high antibiotic cost, increased antibiotic resistance, and potential side effects [4]. Therefore, antibiotics are not recommended for routine use in uncomplicated AB patients [5, 6]. Similarly, antiviral therapy, inhaled corticosteroids, inhaled beta agonists, inhaled anticholinergics, oral corticosteroids, antitussives, oral non-steroidal anti-inflammatory drugs, or alternative therapies are also not recommended for routine use in clinical practice for effectiveness and safety concerns [3, 7].

Chinese herbal medicine, an important part of complementary and alternative medicine, has been widely used in the management of AB [8]. However, evidence-based data is still lacking. Tanreqing oral liquid is a new sixth category oral drug of traditional Chinese herbal medicine jointly developed by Henan Xinyi Pharmaceutical Co., Ltd., and Beijing Jifatang Institute of Chinese Medicine. It is primarily composed of Huangqin (Radix Scutellariae Baicalensis), Xiongdanfen (Fel Selenarcti), Shanyangjiao (Cornu Naemorhedi), Jinyinhua (Flos Lonicerae), and Lianqiao (Forsythiae Fructus) and has the effects of clearing heat, detoxifying, resolving phlegm, and suppressing cough and has anti-infection and anti-inflammatory potential [9, 10]. Tanreqing oral liquid is an extension product of Tanreqing injection, which has been widely used in inpatients and emergency patients with bronchitis or pulmonary infections in China [11, 12].

This prospective, multi-center, randomized, double-blinded, parallel-group, placebo-controlled, superiority trial aims to evaluate the efficacy and safety of Tanreqing oral liquid versus placebo oral liquid in the treatment of AB with phlegm-heat obstructing lungs syndrome.

## Methods/design

This study has been authorized by China State Food and Drug Administration (Approval No. 2005L02403) and was registered with the Chinese Clinical Trial Registry (ChiCTR2000040264). The current study protocol (version 3.0, date 30 August 2019) has been reviewed and approved by the Biomedical Ethics Committee of West China Hospital, Sichuan University (Chengdu, China) on 13 April 2020. This study is sponsored by Shanghai Kaibao Pharmaceutical Co., Ltd. (Shanghai, China); however, the sponsor is not involved in the study design, data collection, data management, future data analysis, or data interpretation.

### Patient population and setting

In this trial, AB will be clinically diagnosed based on the predominant cough with or without sputum production, lasting no more than 3 weeks, but with no evidence of medical history, lung exam, or imaging findings suggesting common cold, pneumonia, acute exacerbation of asthma, bronchiectasis, or chronic obstructive pulmonary disease [13]. The traditional Chinese medicine (TCM) diagnosis of phlegm-heat obstructing lungs syndrome will be made according to the Guidelines for Clinical Research of New Chinese Medicine and TCM guideline for AB [14, 15]. The detailed criteria are listed in Table 1. A total of 270 patients will be enrolled from nine study centers across China: (1) West China Hospital of Sichuan University (2) the First Affiliated Hospital of Guizhou University of TCM (3); Ruikang Hospital Affiliated to Guangxi University of Chinese medicine (4); Chinese Medicine Hospital of Shanghai, (5) the First Affiliated Hospital of Hunan University of Chinese medicine (6); Central Hospital of Minhang District, Shanghai (7); Yueyang Hospital of Integrated Traditional Chinese and Western Medicine, Shanghai University of TCM (8); Guangdong Provincial Hospital of Chinese medicine; and (9) Second Affiliated Hospital of Tianjin University of TCM. Eight of them are academic/teaching hospitals. A research assistant in each study center will recruit 30 patients from the outpatients and emergency departments. Patient recruitment is scheduled to begin from November 2020 to December 2021. Figure 1 shows the flow chart of the trial.

**Table 1 Tab1:** Diagnostic criteria for phlegm-heat obstructing lungs syndrome

Category	Symptoms or signs
Main symptoms	Cough, expectoration
Minor symptoms	Fever; sore throat; chest tightness; thirst; yellow urine; dry stool
Tongue	Red tongue with a yellow or yellow greasy coating
Pulse condition	Slippery and rapid pulse

Diagnostic criteria: both main symptoms + at least one of the minor symptoms + appropriate tongue and pulse condition

**Fig. 1 Fig1:**
[figure not shown]
Study flow chart

AB patients aged 18 to 65 years old, with disease course within 72 h, scoring ≥ 6 points in bronchitis severity score, scoring ≥ 4 points in total cough symptom score, with expectoration in TCM symptom score of 6 points or more, will be included in this trial. Patients who have respiratory diseases such as chronic obstructive pulmonary disease, bronchiectasis, asthma, lung cancer, tuberculosis, pneumonia, and lung abscess; who have severe underlying cardiac, cerebral, hematological, hepatic, or renal disorders or other diseases significantly affecting the survival and prognosis, such as cancer; who have used other medicines after disease onset including antibiotics, expectorants, antitussives, systemic or inhaled corticosteroids, inhaled bronchodilators, and similar Chinese medicines; who use an angiotensin-converting enzyme inhibitor in the last 1 month; who is current smokers or recent ex-smokers quitting smoking less than 1 month ago; whose body temperature is 38.5 °C or higher; or whose ALT or AST > 1.5 times of normal upper limit, urine protein >+, serum creatine abnormality, white blood cell count < 3 × 10^9^/L or > 10 × 10^9^/L, and/or neutrophil granulocyte > 80% will be excluded from the trial. The detailed inclusion and exclusion criteria are listed in Table 2.

**Table 2 Tab2:** Patients’ inclusion and exclusion criteria

**Inclusion criteria**	
1. Diagnosis of acute bronchitis	
2. Phlegm-heat obstructing lungs syndrome in traditional Chinese medicine Zheng	
3. Total cough symptom score ≥ 4 points	
4. Expectoration in traditional Chinese medicine symptom score ≥ 6 points	
5. Bronchitis severity score ≥ 6 points	
6. Disease course within 72 h	
7. Aged 18 to 65 years old	
8. Voluntarily provide written and informed consent	
**Exclusion criteria**	
1. Patients with respiratory diseases such as chronic obstructive pulmonary disease, bronchiectasis, asthma, lung cancer, tuberculosis, pneumonia, lung abscess, and chest X-ray showing lung inflammation lesions	
2. Patients with severe underlying cardiac, cerebral, hematological, hepatic, or renal disorders or other diseases significantly affecting the survival and prognosis, such as cancer	
3. Current smokers or recent ex-smokers quitting smoking less than 1 month ago	
4. Use of an angiotensin-converting enzyme inhibitor in the last 1 month	
5. Patients with body temperature ≥ 38.5 °C	
6. ALT or AST > 1.5 times of normal upper limit, urine protein >+, serum creatine abnormality, white blood cell count < 3 × 10^9^/L or > 10 × 10^9^/L, and/or neutrophil granulocyte > 80%, or those who need antibiotic therapy	
7. Those who have used other medicines after disease onset including antibiotics, expectorants, antitussives, systemic or inhaled corticosteroids, inhaled bronchodilators, Chinese medicines of relieving exterior syndrome with pungent-cool drugs, clearing away heat, and detoxification and other related Chinese medicines	
8. Pregnant or lactating women and those who have pregnancy plans in the last 3 months	
9. Allergic constitution or known to be allergic to any ingredients in tested drug	
10. Mental patients or legal disability	
11. Patients who have participated or are currently participating in another clinical trial in the last 1 month	
12. Patients who are inappropriate for participation judged by researchers	

### Withdrawal and termination criteria

Researchers can withdraw participants for the following reasons: (1) patients’ body temperature rises to 39 °C or more suggesting that other treatments may be needed (2); patients’ symptoms significantly worsen after three treatment days, in this case, trial drugs may need to be stopped and other treatments may need to be provided (3); patients develop serious adverse events (SAEs) or allergic reaction (4); patients accompany with severe comorbidities or complications (5); patients use forbidden medications; and (6) blindness is broken or need to be uncovered urgently for certain reasons. Participants themselves can voluntarily withdraw from the study at any time for any reason. In this case, researchers will make efforts to know and record their withdrawal reasons as much as possible, such as poor efficacy, intolerable to certain adverse reactions, economic factors, lost to follow-up without explanation, or other reasons for dropout.

National Pharmaceutical Supervisory and Administrative Department can terminate the whole trial for any reason. The primary investigators may terminate or suspend the study due to SAEs, poor efficacy, or significant deviation from the protocol during the study. The sponsors can also terminate the study because of SAEs or poor efficacy.

### Randomization and blinding

Central stratified block randomization method will be used in this trial. Two columns of 270 random arrangements of treatments (trial drugs and placebo drugs ratio of 2:1) will be generated by an independent statistician using the Statistical Analysis System (SAS 9.4). The treatment allocation table will be completed after blinding, corresponding to the sequential numbers 001 to 270. An appointed drug administrator will issue drugs according to the drug number. The blinding process should be recorded in writing and signed by all blinding personnel. Actual treatment allocation of trial drugs and placebo drugs will be sealed and stamped on the spot, in duplicate, and saved by the drug clinical trial institution and the sponsor. Trial participants, investigators, and research assistants together with statisticians will be all blinded to treatment allocation throughout the study. If there are serious complications or adverse events during the trial, which affect the trial conduct and the choice of treatment measures, the blind can be broken urgently with the consent of the primary investigator. The reason, time, place, and signature of uncovering the blind will be recorded in detail.

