### Statistical analysis

The full analysis set (FAS) population will include all randomized participants who receive at least 20 mL trial medication and collect outcome data after treatment. It will be used to describe the analysis set which is as complete as possible and as close as possible to the intention-to-treat ideal of including all randomized participants. Per-protocol (PP) population will include all randomized patients who strictly follow the protocol. The safety set (SS) population will include all randomized participants who receive at least 20 mL trial medication and have safety evaluation data. Missing efficacy data will be imputed using the last observation carried forward method. Efficacy and safety analysis will be performed based on the FAS and PP population and SS population.

Statistical analysis will be performed using SAS 9.4 according to the statistical analysis plan. The primary outcome of cough resolution rate will be analyzed using the chi-squared or Fisher’s exact tests. Furthermore, logistic regression will be conducted to provide a risk ratio. For secondary outcomes, *t* test and nonparametric tests will be used for quantitative data, and chi-squared or Fisher’s exact tests will be used for qualitative data. A one-sided *P*-value of 0.025 or less will be considered statistically significant.

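### Allocation is stratified, but the tests named for the primary and secondary outcomes ignore the strata; this is conservative and costs some power if the strata are prognostic

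*Protocol article*

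**What the plan says.** All places are in the protocol article.

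- **Randomization and blinding:** "Central stratified block randomization method will be used in this trial", with a "trial drugs and placebo drugs ratio of 2:1". The section does not say what the strata are.
- **Patient population and setting:** there are nine centres, and "A research assistant in each study center will recruit 30 patients". This makes centre the natural candidate for the stratum, but the text does not say so.
- **Statistical analysis, primary outcome:** "The primary outcome of cough resolution rate will be analyzed using the chi-squared or Fisher’s exact tests". Then: "Furthermore, logistic regression will be conducted to provide a risk ratio". No covariates are given for that model.
- **Statistical analysis, secondary outcomes:** the t "test and nonparametric tests will be used for quantitative data, and chi-squared or Fisher’s exact tests will be used for qualitative data".
- **Statistical analysis, reference to the SAP:** "Statistical analysis will be performed using SAS 9.4 according to the statistical analysis plan". That plan is not available here.

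Significance is judged at a one-sided P of 0.025. No confidence intervals are specified.

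**The concern.** Stratified allocation balances the arms within each stratum, so differences between strata drop out of the treatment contrast. An unstratified test still counts those differences in its standard error. If the strata predict outcome, that standard error is too large for the design, the P-value is too large, and power is lower than the same data could give.

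The assumption that centres are prognostic is plausible here, though not documented. Patients come from outpatient and emergency departments at nine hospitals, cough is self-rated, and the bronchitis severity score is observer-rated and includes auscultation.

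The stake is efficiency, together with having one pre-specified primary test. If the choice between a stratified and an unstratified result is left open until the data are known, it can be questioned later.

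**Working it through.** **1. The plan's own figure.** The sample size section uses a one-sided alpha of 0.025, power 0.80, rates 0.80 and 0.40, margin 0.2 and K = 2:

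n_C = (1.960 + 0.842)² / (0.8 − 0.4 − 0.2)² × [0.8×0.2/2 + 0.4×0.6] = 7.849 / 0.04 × 0.32 = 62.79, rounded up to 63.

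The stated 63 (and 126 on active treatment) reproduces. The formula contains no between-stratum variance, so this point does not change it.

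**2. Assumptions.** The article gives neither the factor nor its effect, so I assume:
- the strata are the nine centres, each with 20 active and 10 placebo patients (180/90 in all);
- centre effects are normal on the logit scale, with SD 0, 0.3, 0.5 or 1.0.

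For scale, take a typical placebo rate of 40% (logit −0.405). SD 0.5 puts 95% of centres between −0.405 ± 0.98, that is 20% to 64%. SD 1.0 gives −0.405 ± 1.96, that is 9% to 83%.

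**3. Why the test is conservative.** Under the null, the chi-squared variance uses p(1−p), which equals the mean within-centre variance plus the variance of the centre rates. Only the within-centre part affects the balanced contrast. With p = 0.40, p(1−p) = 0.24.

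- SD 0.5: the variance of the centre rates is about 0.013. The true SE is √(1 − 0.013/0.24) = 0.973 of the SE used, so the error is P(Z > 1.96/0.973) = 0.022.
- SD 1.0: the variance is about 0.041. The ratio is √(1 − 0.041/0.24) = 0.911, so the error is P(Z > 1.96/0.911) = 0.016.

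**4. Simulation.** 40,000 trials per scenario, one-sided 0.025, with average rates held at the values shown. Each cell gives unstratified / stratified; the stratified test is Cochran-Mantel-Haenszel (CMH) in the first two result columns and uses a stratified SE in the last.

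| Centre SD | True alpha, null at 40% | Power, 60% v 40%, zero-difference test | Power, 80% v 40%, 0.2-margin test |
|---|---|---|---|
| 0 | 0.0250 / 0.0247 | 0.879 / 0.878 | 0.912 / 0.910 |
| 0.3 | 0.0236 / 0.0242 | 0.882 / 0.883 | 0.913 / 0.915 |
| 0.5 | 0.0222 / 0.0250 | 0.890 / 0.896 | 0.909 / 0.916 |
| 1.0 | 0.0159 / 0.0240 | 0.902 / 0.928 | 0.904 / 0.929 |

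Repeat runs gave a chi-squared alpha of 0.021 to 0.022 at SD 0.5 and 0.016 to 0.017 at SD 1.0. For 80% versus 40%, the zero-difference test has power 1.000 with either method at every SD.

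**5. A smaller effect.** A within-centre log odds ratio of 0.7 takes 40% to 57%, a difference of 17 points. Power, chi-squared against CMH:
- SD 0.5: 73.5% v 74.5%, a loss of 1.0 point;
- SD 1.0: 62.9% v 68.9%, a loss of 6.0 points.

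At a fixed odds ratio the average risk difference shrinks as the SD grows. The loss due to ignoring strata is therefore the gap within each row, not the fall from one row to the next.

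**6. A caution on the margin column.** When the average difference is exactly 0.20, the simple Wald margin tests reject 2.75% (unstratified) and 2.97% (stratified) of the time at SD 0.5, and 2.67% and 3.38% at SD 1.0. Part of the stratified gain of 0.6 to 2.5 points therefore reflects a difference in size, and 2.5 points is best read as an upper figure for this scenario.

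**The case against.** The strongest objection is that adjustment for strata is commonly left to the SAP. The article refers to one, and the logistic regression could already contain the stratum. This stands in part: the unseen plan may have dealt with the matter, and the finding covers only the tests that the article names. But the article does more than stay silent. It commits to particular tests for the primary and secondary outcomes, and it presents the regression as an addition that supplies an effect estimate. An SAP that stratified the primary test would differ from this text.

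It is also fair to object that the stratification factor and its prognostic strength are unknown. If the strata do not predict outcome, the mismatch costs nothing, as the SD 0 row shows.

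A reader might infer three stronger things, none of which the document supports:

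- **That the primary test is invalid or gives false positives.** Ignoring the strata moves the error rate down, so a positive chi-squared result is not undermined.
- **That the plan's confidence intervals are wrong.** The article specifies none.
- **That the trial is seriously underpowered for this reason.** A loss of about 13 points (49.2% v 61.9%) appears only with centre SD 1.5 and log odds ratio 0.7. That SD means 95% of centres with placebo resolution anywhere from 3% to 93%. The effect is also below the 20 points that the sample size section treats as clinically significant. Nothing in the article points to such a spread.

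**Conclusion.** The mismatch is in the text: allocation is stratified, and the named tests are not. Its consequence is modest and runs in the safe direction.

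- With nine centres as the assumed strata, the nominal one-sided 0.025 becomes about 0.021 to 0.022 at SD 0.5 and 0.016 to 0.017 at SD 1.0.
- At the planning rates the zero-difference test loses no power, and a test against the 0.2 margin loses about 0.6 to 2.5 points over the same SD range.
- For effects near 17 to 20 points the loss is about 1 point or less at SD 0.5. At SD 1.0 it is 2.7 points for the 20-point effect and 6.0 points for the 17-point effect.

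These sizes rest on the assumed factor, equal centres of 30, normally distributed logit effects, and all 270 patients analysed. This is a free improvement rather than a threat to validity. Confidence is medium because the SAP is not shown.

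**What to change.** 1. Name the stratification factor in the protocol and the SAP.
2. Make the primary analysis stratified by that factor: a CMH test for zero difference, and a Mantel-Haenszel or stratified Miettinen-Nurminen risk difference with a 95% CI, which can also be read against the 0.2 margin.
3. Include the factor in the logistic regression and in the models or tests for the secondary outcomes.
4. Keep the unstratified chi-squared test as a sensitivity analysis.
5. If the SAP already does this, bring the article's wording into line with it.

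The cost is wording only: no extra patients, visits or data. The change should be fixed before unblinding. If it counts as a significant change to the data analysis, the article's own procedure requires a signed modification and renewed ethics committee approval.

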### Interventions

All patients will be randomly allocated to either the Tanreqing group or the placebo group. Patients in either group will receive Tanreqing oral liquid or placebo liquid, 20 mL three times daily for seven consecutive days. Figure 2 provides the details of the study procedures.

**Fig. 2 Fig2:**
[figure not shown]
Schedule of study procedures. TCM, traditional Chinese medicine; VAS, visual analog scale

#### Concomitant treatments and forbidden medication

Medications used to control the underlying diseases such as hypertensive or diabetic mellitus, will be permitted, but newly use of angiotensin-converting enzyme inhibitors will not be allowed. Chinese medicine and other Western medicine that may relieve cough or sputum will not be permitted for potential impact on the efficacy and safety analysis. Antibiotics, expectorants, or antitussives can be taken in combination only when patients’ conditions significantly worsen. All used medications should be recorded in the original research medical records, including name, dose, mode of administration, and treatment duration.

